**Methods:**

This study adopts a mixed-method design to estimate the treatment effect using variables generated from historical data of Ghana and Kenya Demographic and Health Survey data sets of 2008/2014, as treatment and comparison groups respectively. As DHS uses complex design, weighting will be applied to the data sets to cater for clustering and stratification at all stages of the analysis by setting the data in STATA and prefix Stata commands with *‘svy’*. Thus, the policy impact will be determined using quasi-experimental designs; propensity score matching, and difference-in-differences methods. Prevalence, mean difference, and test of association between outcome and exposure variables will be achieved using the Rao Scot Chi-square. Confounding variables will be adjusted for using Poisson and multiple logistics regression models. Statistical results will be reported in proportions, regression coefficient, and risk ratios. This study then employs intrinsic-case study technique to explore the current operations of the ‘free’ policy in Ghana, using qualitative methods to obtain primary data from the Upper East Region of Ghana for an in-depth analysis.

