### Sample weighting

Due to the complex nature of the two-stage sampling design, which essentially produces a complex survey data sets, sample weighting will be applied across the data sets, to cater for clustering (the enumeration areas) and stratification (urban/rural area of residence) for precision. Sample weighting will be set in STATA 15 software, using variable *v021* and v022 from the data sets, as primary sampling units and strata respectively. Thereafter, all commands will prefix the svy (survey) to apply sample weighting in the analysis*.*

The choice of rural/urban area of residence allows for socio-economic variation to be incorporated into the data composition and analysis. Hence, robust standard error (Taylor Linearization and bootstrapping) approach will be used to adjust for clustering and stratification bias.

Sample probability weighting will be generated through the selection of sample weighting variable *v005* from the data sets and divided by 1000,000, to cater for the 6 decimal places, usually not reported in Demographic and Health Survey data, thus, stata command of;

*gen wgt* = *v005/100,000,* then, *svyset [pw* = *wgt], psu (v021) strata (v022) to set the DHS data.*

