Logistics regression is considered appropriate, giving the binary status variables of interest; antenatal care up-take [yes = 1 (ANC visit ≥ 4)] and [no = 0 (ANC visit of ≤ 3]; facility delivery utilization [yes = 1 (facility delivery) and no = 0 (home delivery)], and the secondary outcome variables; stillbirth, perinatal and neonatal deaths, generated through the re-coding of the relevant variable *m14, m15, b6, b7*, and *s1015,* from the DHS data sets (Table 5).

The treatment difference will be determined through nearest-neighbor matching of treated and untreated units’ propensity scores generated ex-post, and using logistics regression while controlling for the confounding variables for precision. The 'free' policy impact will then be determined using the average treatment effect on the treated. Robustness of results will be achieved with reduced standard errors using bootstrapping replication while testing for sensitivity using a t-test of bias, and probit regression.

Of the treatment and comparison country analysis, the DID analysis will be used to determine the policy impact, using the 2008 data set of the two countries (Ghana and Kenya) as a baseline and 2014 data sets as the end line. The study is powered by the sample size calculation, originally determined by the survey design. The sample size is n = 2992/5884 (8,876) for Ghana DHS 2008/2014 data sets, and n = 6079/20,964 (27,043) for Kenya DHS 2008/2014 data sets respectively.

Clustering and stratification will be adjusted for using sample survey weighting at all stages of the analysis. This will produce unbiased treatment estimate that can be generalized to the original survey population [26, 52].

The qualitative data will be deductively analyzed using predefined themes. However, common themes that emerges from the interviews and focused discussion will be organized as sub-themes and inductively reported. The approach will be aided by NVIVO 12, through which nodes and their children will be created to categories significant statements into similarities and dissimilarities [73].

The results of the primary data will be reported using the common themes approach with word frequency count and cloud, and vivid quotations to back themes. The inclusion of qualitative data will add context and situate the discussion with explanatory power to the statistical findings [48].

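### The svy prefix, the only weighting route stated, cannot reach the nearest-neighbour matching ATT, so the claim that weighting makes the treatment estimate unbiased and generalizable is unsupported for it

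*Protocol article*

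**What the plan says.** Three statements in the protocol article have to be read together.

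- **Scope of weighting.** Data analysis: "Clustering and stratification will be adjusted for using sample survey weighting at all stages of the analysis". The next sentence states the property this is meant to secure: "This will produce unbiased treatment estimate that can be generalized to the original survey population".
- **Mechanism.** The Abstract (Methods) says weighting is applied "at all stages of the analysis by setting the data in STATA and prefix Stata commands with" svy. Sample weighting builds a probability weight from v005, declares v021 as PSU and v022 as stratum, prints the svyset line, and adds: "Thereafter, all commands will prefix the svy (survey) to apply sample weighting in the analysis". No other mechanism is given.
- **Matching estimator.** Data analysis: "The treatment difference will be determined through nearest-neighbor matching of treated and untreated" units' propensity scores, after which the "policy impact will then be determined using the average treatment effect on the treated". Standard errors come from bootstrap replication. No matching command is named, and nothing says how v005 enters the propensity model, the matched average or the bootstrap.

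Matching uses the merged Ghana 2008 and 2014 files. The DID analysis, which uses Ghana and Kenya, is also said to determine the policy impact.

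**The concern.** The svy prefix works with estimation commands written for survey data, such as logistic and Poisson regression. Nearest-neighbour matching commands are not run under it. This is general knowledge of the software and not a statement in the article. It means that an instruction given for all commands cannot be carried out for one of the two estimators of policy impact. Weighting only the logistic propensity model would not close the gap, because the ATT is formed afterwards as an average over treated births, and that average needs the weights too.

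Two things are at stake. First, the article intends to draw conclusions for policymakers, so it matters whether the ATT describes women in Ghana or only the women in the file. Second, Statistical methods and rationale relies on DID and matching to offset each other's limitations. If one is weighted and the other is not, they refer to different populations, and part of any disagreement could come from weighting alone.

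A second problem needs no software knowledge. Sampling weights address who is represented. They do not remove confounding, so they cannot by themselves make a treatment estimate unbiased.

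**Working it through.** **1. The plan's own figure.** Merged Ghana sample: 2992 + 5884 = 8876, as stated. The article gives no population shares, no stratum-specific effects and no distribution of v005, so the size of the problem cannot be computed from it.

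**2. What the weights do to a matched ATT.** Let d_i be the outcome of treated birth i minus that of its match, and w_i its v005 weight.

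- Sample ATT: sum(d_i) / N_treated
- Population-representative ATT: sum(w_i × d_i) / sum(w_i)

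A constant multiplier of w cancels. The mismatch in Sample weighting between the text (division by 1000,000) and the command (division by 100,000) therefore does not affect this point.

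**3. Difference between the two.** With two groups, urban and rural,

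unweighted − weighted = (s − π) × (ATT_urban − ATT_rural),

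where s and π are the urban shares among *treated* births in the file and in the population. The difference is zero if the effects are equal or if s = π.

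**4. Illustration.** The article's one figure on the make-up of the Ghana sample is 216 urban and 211 rural clusters in 2014, so s = 216/427 = 0.506. Using a cluster share for the share of treated births is an assumption. The values of π and the effect differences are also assumed. Shifts are in percentage points:

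| π (assumed) | ATT difference 0 | 5 points | 10 points | 20 points |
|---|---|---|---|---|
| 0.35 | 0 | 0.78 | 1.56 | 3.12 |
| 0.40 | 0 | 0.53 | 1.06 | 2.12 |
| 0.45 | 0 | 0.28 | 0.56 | 1.12 |
| 0.506 | 0 | 0 | 0 | 0 |
| 0.55 | 0 | −0.22 | −0.44 | −0.88 |

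Example: (0.506 − 0.35) × 10 = 1.56. All signs reverse if the larger effect is rural.

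**5. Simulation check.** Nearest-neighbour matching within urban and rural strata, n = 8876, 100 replicates, sample urban share 0.506, overall urban share in the population assumed 0.35, treatment assumed more common in urban areas:

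| Assumed ATT urban / rural | Unweighted | Weighted | Target |
|---|---|---|---|
| 10 / 10 | 10.03 | 10.06 | 10.00 |
| 5 / 15 | 9.72 | 11.24 | 11.06 |
| 0 / 20 | 9.02 | 12.23 | 12.13 |

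The weighted mean recovers the target. The unweighted mean does so only when effects are equal. Across the equal-effect runs, including those at other population shares, estimates missed 10 by up to 0.24 points, which indicates the simulation noise.

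**6. The word unbiased.** Study design says matching assumes that unobserved characteristics are similar and cancel out. Statistical assumptions repeats that there are no systematic unobserved differences, and gives parallel trends for DID. Scope and limitations names the absence of randomization as a limitation. Against these, Data analysis credits weighting itself with producing an unbiased estimate. The first three make freedom from bias conditional on assumptions about unobserved factors and trends, which no sampling weight can supply.

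**The case against.** The strongest reply is that the article says weighting applies throughout, names no matching command, and creates an explicit weight variable that could enter the matched average directly. How it enters is detail that a condensed article may leave to the full protocol. This stands to a point: a reader might infer that the ATT is definitely unweighted, and no sentence says so. It does not dispose of the concern, because the article does more than omit a detail. It fixes one mechanism for all commands and asserts a property of the result, and both can be judged as written.

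A reader might also infer that the matched ATT over-represents oversampled groups, or is too high. The article names no oversampled group in Ghana and gives no population share. Use of v005 implies unequal selection probabilities, but neither direction nor size follows, and bias also requires effects that differ between the groups. That objection stands in full.

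Parts of a remedy are already present. Region and rural/urban residence are listed under Covariates, though subject to a significance screen. Bootstrapping is mentioned under Sample weighting as an adjustment for clustering and stratification, though without a resampling unit. The assumptions behind matching are disclosed elsewhere, which softens the word unbiased but does not make the sentence correct.

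**Conclusion.** The concern holds for the matching ATT. Under the stated mechanism that estimate would be a sample average, and the claim that it generalizes to the survey population is unsupported. The weighted regressions and the DID, which also determines the policy impact, are outside the weighting gap.

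The size is unknown. It is zero if the effect is homogeneous or if the file and population shares of treated births agree. Under the assumed values above it ranges up to about 3 percentage points and can take either sign. This rests on the general fact that the svy prefix does not cover matching commands and, for any actual bias, on effects that vary with selection probability.

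The statement that weighting yields an unbiased treatment estimate is wrong for any of the analyses, whatever the software does.

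**What to change.** In Data analysis, state the following for the matching ATT:

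1. Include v005, region and rural/urban residence in the propensity model, kept whatever the significance screen shows.
2. Compute the ATT as the v005-weighted mean, over treated births, of own outcome minus matched outcome.
3. Obtain its interval by resampling whole PSUs within strata, repeating the propensity model and the matching in each replicate.

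If this is not wanted, call the result a sample ATT and withdraw the generalizability claim for it.

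In either case, replace the words unbiased treatment estimate by: *representative of the surveyed population (when weighted), subject to the matching and DID assumptions*.

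The cost is a few lines of code and two or three sentences, using variables the article already names. The downside is a slightly wider interval.

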## Discussions

The study design and methodology will be discussed as deliverables outlining the methodological strength and limitations for future researchers. Multistage discussions will be employed adequately and distinctly, in reporting the study findings. The predictive abilities of the variable and the covariates in the multiple logistic regression model will be thoroughly examined along the lines of statistical significance levels, set at p < 0.05. The study discussion will also compare and contrast the current result with exiting literature for congruence or divergence.

The effects of facility delivery utilization i.e. antennal clinic attendance and health facility delivery will be discussed in the context of financial accessibility and universal health coverage. Stillbirth and perinatal deaths outcomes will be modeled to make predictions and projections in the discussion stage and inferred on targets such as achieving sustainable development goal 3.

The discussion will also look at the ‘free’ policy effectiveness and impact, drawing lessons from the qualitative result in the context of lower/middle income country, and the overall objectives of social health insurance in developing country context to inform policy development in other countries, particularly, Sub-Saharan Africa.

In the qualitative stage, discussions will follow the thematic inductive approach, where meanings from participants’ views are compared to existing literature to establish similarities and dissimilarities. The discussions are expected to identify policy implications from the results to inform practice and research. Discussions will isolate key study findings and highlight the contribution of the study to knowledge and policy, i.e. what is known from the study, in an attempt to address the research objectives and gaps.

Conclusions will be drawn for policymakers and recommendations made for policy, practice, and research. Within the study context, the conclusions will take the shape of the data as it is compared to existing literature, mirroring Lipsky's theory of Street-Level Bureaucracy to draw lessons for future design and implementation of a similar intervention in similar settings.

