### Kenya as a comparison country

Comparatively, Kenya showed relevant commonalities as Ghana and was chosen as a comparison country. First, Kenya DHS data were collected about the same time as Ghana and had no such intervention within the time frame. This is necessary for the DID analysis.

Secondly, the DHS reports of the two countries show similarities of related variables of interest in this study. For example, Ghana recorded 30 and 50 per 1000 live births for neonatal and infant mortality rates respectively, and within the same period, Kenya also recorded 31 and 52 per 1000 live births for neonatal and infant mortality, according to their respective 2008 DHS reports [59–61].

Also, Kenya was considered appropriate giving its geopolitical and socioeconomic similarities to Ghana such as; political stability, literacy rate, lingua franca, and Sub-Saharan location.

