### Exposure variables

The National Health Insurance status [proxy to the ‘free’ maternal healthcare policy (FMHCP)] is the main exposure variable. However, on the secondary level of analysis, antenatal care up-take (binary) and facility delivery utilization (also binary) are independent predictors, through which the secondary outcomes of interest; stillbirth, perinatal death, and neonatal death can be measured.

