### Protocol implementation

This protocol will be implemented in phases as per the design. Proposal writing preceded the protocol’s approval and the approved protocol will be implemented as outlined in Table 6 (see Additional file 1). The implementation will also be monitored by the Ghana Health Service Ethics Committee, as well as the supervisory committee of the University of Ghana Public Health School. The approved protocol follows the standard of research required for the award of a doctoral degree set out by the University of Ghana.

**Table 6 Tab6:** Protocol implementation, monitoring & evaluation

Phase I	Phase II	Phase III
*Review of relevant literature on;* Maternal health care policy Maternal health care utilization Burden of stillbirths Perinatal deaths Neonatal mortality *Retrieval of secondary data from MEASURE DHS;* Ghana DHS 2008 Ghana DHS 2014 Kenya DHS 2008 and Kenya DHS 2014 *Cleaning and organization of DHS data:* Dropping of irrelevant variables Merger of data sets *Variable management* recoding and renaming *Preliminary analysis of DHS data (secondary data)* Hypothesis testing Analysis of association and Determination of significant levels (set at ≤ 0.5)	Gaining entrée for primary data collection *Primary data collection* In-depth interviews (IDIs) of service providers Focus Group Discussion (FGD) among pregnant women *Preliminary analysis of qualitative data* Data transcription Annotation of significant statement Coding and Categorization of common themes *Key Informant Interviews* Transcription of key informant interviews *Triangulation of data* Drawing congruence of policy user Perspective/perception, Service provider perspective and Policy implementers view points	*Presentation of preliminary findings and feedback at;* Institutional level Clinical forum ANC clinic to policy users *Summary presentation at;* Regional Annual Performance Review *Presentation of final report at;* School of Public Health, University of Ghana *Publication of Final report for policy actors, research and scientific community in;* MOH reports NHIA report Internal journals Local journals Policy briefs
Monitoring and evaluation of phase I, II, and III		
Guidance and comments of Co-investigator 1,2 and 3	Guidance and comments of Co-investigators 1 and 2	Scheduling of presentation Purview of Co-investigators and faculty of Health Policy Planning Management of the University of Ghana Public Health School

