### Data analysis

The secondary data will be cleaned and organized, dropping irrelevant variables and renaming covariates for ease of reference as necessary. Essentially, variables of interest in this study are binary outcomes i.e. 1 = case/the presents of an intervention, and 0 = no case, the absence of intervention, control.

Both multivariate logistic regression and Poisson with robust standard error, or negative binomial regression depending on whether there is over dispersion (conditional variance exceeding the conditional mean) will be fitted and analyzed. Thus, **loge** {*p*1 / *(1—pi)*} = *b0* + *b1 Xi1* + *b2 Xi2* + … + *bkXik*. The Use of the multiple logistic regression model also comes with the advantage of adjusting for confounding by including the covariates in the model.

For the matching method, Ghana’s DHS data sets (2008 and 2014) will be merged. This will increase the sample size to n = 8876, and add power to the study. The merger will also eliminate the risk of lack of common support, the so-called curse of dimensionality, a common phenomenon in propensity score matching, where treated units propensity scores cannot find suitable pairs.

Descriptive data will be presented using tables, frequencies, and proportions. The data will then be analyzed distinctly, using multiple statistical models and quasi-experimental design techniques. Firstly, the student independent *t*-test will be used to test for proportions, the significance of association, and mean differences between the independent variable, and the binary outcomes of interest; antenatal care uptake, and facility delivery utilization.

Test of association set < 0.05 less of significance, between the secondary variables of interest (stillbirth, perinatal death, and neonatal mortality) and the covariates; mothers age, marital status, level of education, wealth index, region, area of residence, twin delivery, parity, and employment status will be determined by using the Rao Scot Chis-square, which has an added sensitivity advantage, while adjusting for complex survey design features (weighting, clustering and stratification).

Only covariates found to be significantly associated with the dependent or independent variables will then be included in a multiple logistic regression model and adjusted for confounding [72].

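### The Discussions section judges predictive ability by p < 0.05, which does not measure prediction; report adjusted estimates with confidence intervals instead (minor)

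*Protocol article*

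**What the plan says.** The Discussions section states this criterion: "predictive abilities of the variable and the covariates in the multiple logistic regression model will be thoroughly examined along the lines of statistical significance levels", and fixes the level: "along the lines of statistical significance levels, set at p < 0.05". It treats the exposure and the covariates alike. The same section says that stillbirth and perinatal death will be modelled for predictions and projections, set against targets such as SDG 3.

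Under Data analysis, a significance screen already decides which covariates enter: "Only covariates found to be significantly associated with the dependent or independent variables will then be included in a multiple logistic regression model". There and under Covariates, the stated reason for including them is adjustment for confounding.

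The Abstract promises proportions, regression coefficients and risk ratios, but the Discussions sentence does not tie predictive ability to any of these. The article names no measure of discrimination or calibration.

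**The concern.** The sentence names a property, predictive ability, and a yardstick for it, p < 0.05, that does not measure it. This is a stated criterion, not a detail left to a fuller plan. Followed as written, it would sort factors into predictors and non-predictors of stillbirth, perinatal and neonatal death by a rule that can give different answers for the same strength of association, depending on how many deaths are in the data. Factors that barely shift a birth's predicted risk could be called predictors, and real but weaker factors could be dismissed.

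The covariates are also in the model to de-confound the exposure. Their own coefficients are not adjusted for whatever confounds them, so a significant covariate is not thereby an effect or a lever for policy. The article directs its conclusions to policymakers, so the labels matter for what readers take away.

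**Working it through.** **Inputs from the article**
- Ghana sample: "The sample size is n = 2992/5884 (8,876) for Ghana DHS 2008/2014 data sets". The sum reproduces: 2,992 + 5,884 = 8,876. The article makes this merger for the matching analysis; I assume that the logistic covariate models use the same records.
- Death rate: "Ghana recorded 30 and 50 per 1000 live births for neonatal and infant mortality rates respectively" (Kenya as a comparison country). I use 30 per 1000, i.e. 3%, with 2% to 4% as an assumed range, because no stillbirth or perinatal rate is given for these data sets.
- Level: 0.05, taken as two-sided. Table 6 has "Determination of significant levels (set at ≤ 0.5", probably a slip, which should be reconciled with the 0.05 given elsewhere.

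**Assumptions of mine:** one binary factor, held by 50% of survivors (range 10% to 50%); design effect (deff) 1 to 2.

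**Formulas.** With D deaths, S survivors, q the share of deaths exposed and p the share of survivors exposed:
- SE = √[deff × p̄(1 − p̄)(1/D + 1/S)], where p̄ is the pooled exposure share
- just significant when q − p = 1.96 × SE
- OR = [q/(1 − q)] / [p/(1 − p)]
- AUC of this one factor = 0.5 + (q − p)/2

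**1. What just passes, merged Ghana data.** D = 0.03 × 8,876 ≈ 266 and S ≈ 8,610.
- deff 1: SE = √[0.25 × (1/266 + 1/8,610)] ≈ 0.0311; q − p = 0.061; q = 0.561; OR 1.28; AUC 0.530.
- deff 2: SE ≈ 0.0311 × 1.414 = 0.0440; q − p = 0.086; q = 0.586; OR 1.42; AUC 0.543.

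Over death rates of 2% to 4% and prevalences of 10% to 50%, the just-significant AUC runs from 0.516 to 0.553, where 0.5 is no separation.

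As risks, with deff 1:
- exposed: 0.03 × 0.561 / (0.03 × 0.561 + 0.97 × 0.5) ≈ 33.5 per 1000
- unexposed: 0.03 × 0.439 / (0.03 × 0.439 + 0.97 × 0.5) ≈ 26.4 per 1000

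**2. What is missed.** For OR 1.2, q = 1.2/2.2 = 0.545, so q − p = 0.045. The chance of p < 0.05 is Φ(z − 1.96).

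| deff | z | Chance of p < 0.05 |
|---|---|---|
| 1 | 1.46 | 0.31 |
| 1.5 | 1.19 | 0.22 |
| 2 | 1.03 | 0.18 |

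**3. Same factor, different data.** For OR 1.5, q = 0.6 and AUC = 0.550 whatever the sample size. The Ghana 2008 survey alone is used here only to illustrate.

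| deff | p-value, Ghana 2008 alone (n = 2,992) | p-value, merged Ghana (n = 8,876) |
|---|---|---|
| 1 | 0.062 | 0.0013 |
| 1.5 | 0.13 | 0.0087 |

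The verdict changes; the separation of deaths from survivors does not.

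**The case against.** The strongest reply is that predictive is used loosely for associated. The goal, objectives, research questions and hypotheses concern association and treatment effect; none asks for individual risk prediction. The policy impact rests on the average treatment effect on the treated and on the difference-in-differences estimate. The planned projections concern a national rate (the plain language summary names 12 per 1000 live births), which a c-statistic would not assess. Coefficients and risk ratios will be reported, so readers will see effect sizes. The sentence also covers the logistic models for antenatal care and facility delivery, where events are not rare and the figures above do not apply.

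Most of this stands, and it makes the point small. It does not remove it: the sentence still makes significance the test of predictive ability, and reporting risk ratios elsewhere does not change that rule.

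Two cautions about size also stand. A single-factor AUC is low even for a strong factor: at OR 2.0 and 50% prevalence, q = 0.667 and the AUC is only 0.58. And an odds ratio near 1.4 for death is not trivial for public health. The AUCs above show that passing 0.05 is not evidence of prediction; they do not show that the factors are unimportant.

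Three stronger readings are tempting but unsupported:
- A reader might pool all four surveys (8,876 + 27,043 = 35,919) and argue that far weaker factors pass. No section plans a covariate model of that size. Under Data source and size, cross-country analysis is tied to the difference-in-differences method, and Data analysis merges only Ghana's surveys.
- A reader might treat "facility delivery utilization (also binary) are independent predictors" under Exposure variables as the same error. There it is only a label for explanatory variables.
- A reader might say that p-values mainly reflect sample size. They also depend on effect size, prevalence, number of deaths and clustering, and in the Ghana data weak factors would more often miss significance than reach it.

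**Conclusion.** The point holds, with low importance. Significance at 0.05 is the wrong criterion for predictive ability. In the merged Ghana data it would admit a factor with an odds ratio of about 1.28 to 1.42 and an AUC of about 0.53 to 0.54, and would usually miss one with an odds ratio of 1.2. These figures rest on 3% deaths (the article's neonatal rate), 50% prevalence, a design effect of 1 to 2, a single unadjusted binary factor, and logistic models fitted to the 8,876 merged records. Other assumptions move the figures but not the conclusion.

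A reader might infer that the policy-effect estimates are compromised. They are not: neither the matching nor the difference-in-differences estimate depends on this sentence. What changes is what the discussion may say about individual factors.

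**What to change.** Replace the sentence in the Discussions section so that:
- the exposure's adjusted risk or odds ratio is reported with its 95% confidence interval in each model;
- covariates are described as adjustment variables, and their coefficients are not interpreted as effects;
- no claim of predictive ability is based on p < 0.05.

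Only if a prediction claim for a death model is really intended, add a survey-weighted c-statistic and calibration with internal validation for that model.

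The cost is one sentence and no new data; the optional part is a further step after model fitting. The price is weaker claims about individual covariates.
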